The primary outcome for a future definitive randomized controlled trial comparing goal-oriented weight reduction with liraglutide together with risk factor modification group to risk factor modification alone will be the effect on AF-free survival at 52 weeks following AF ablation. Such a study cannot be adequately designed without evidence that liraglutide can achieve weight loss in this cohort between identification of the need for ablation and the procedure (on average 13 weeks), that adherence is maintained before and after ablation, and that recruitment rates are sufficient. This knowledge is essential to design a future definitive trial.

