### Intervention

As per British National Formulary, liraglutide will be injected 0.6 mg once daily, increased in steps of 1 week up to a maintenance dose of 3 mg once daily, or the maximally tolerated. If still clinically indicated at the end of study, liraglutide will be continued and followed up as per the National Health Service (NHS) standard care. This will be reported as cumulative doses of liraglutide over the study period, considering any disruption due to potential side effects. Adherence will be checked during monthly telephone follow-ups and return of empty pens via pre-paid envelopes from the participants.

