### Feasibility outcome measures

The study will be considered feasible if as follows:Recruitment rate ≥ 50% (≥ 30 patients) of those eligible (56 patients per year), drop-out rate < 10%, and data completeness ≥ 90%Adherence to medication rate ≥ 70% in the participants at the end of study [23]. Adherence will be measured by the proportion of patients who tolerate total cumulative dose of 657 mg and more of liraglutide at 1 year (minimal maintenance dose of 1.8 mg over 365 days).Weigh loss at least 5% from baseline in ≥ 60% participants at the end of study [23, 27]. Body mass change in kilograms and BMI between the baseline, at ablation, and last days of treatment with liraglutide (± 7 days) will be measured using a single set of calibrated scales using a standardized protocol.

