### Statistical analysis

Descriptive statistics will be used to summarize demographics and medical histories. The number of patients recruited over 52 weeks will be reported as a percentage of those eligible. The adherence to the medication will be reported as a proportion of patients who tolerate a total cumulative dose of 657 mg of liraglutide or more over 52-week follow-up period. The cumulative dose of liraglutide will be calculated for each participant, and mean and standard deviation for all participants will be reported. The percentage of change in weight from baseline to the end of follow-up will be calculated for each participant, and the proportion of participants who lost weight ≥ 5% and < 5% will be reported. 

For the secondary outcome measures, descriptive statistics according to the data type will be used to report at each predefined time point (baseline, before ablation, and end of follow-up). Paired *t*-test will be used to compare the changes for continuous variables such as changes in CMR measurements, biomarkers, and electroanatomic data to determine potential mechanistic changes in relation to weight loss. As this is a feasibility study, the analysis will be reported as point estimates and corresponding 95% confidence intervals to provide precision of estimates, and no *p*-values will be reported. A Kaplan–Meier curve will be constructed for time to recurrence of AF at 1 year following ablation. This will be performed in preparation for the calculation of sample size with appropriate power for the future clinical trial based on a time-to-event superiority analysis.

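### The feasibility rule and the stated analysis do not use the pre-ablation phase: adherence is one 657 mg total with no split at ablation, and the 5% weight result is computed only at end of follow-up

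*Protocol article*

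**What the plan says.** The Background of the protocol article lists what must be known before a definitive trial can be designed. The first item is "evidence that liraglutide can achieve weight loss in this cohort between identification of the need for ablation and the procedure", an interval put at 13 weeks on average. The others are "that adherence is maintained before and after ablation, and that recruitment rates are sufficient". Aims and objectives then names percentage weight loss as a primary objective at two times, ablation and end of follow-up. It names adherence as a primary objective through to the end of the year after ablation.

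Feasibility outcome measures gives the decision rule. The adherence mark is 70% of participants, defined so: "Adherence will be measured by the proportion of patients who tolerate total cumulative dose of 657 mg and more of liraglutide at 1 year". The total is explained as "minimal maintenance dose of 1.8 mg over 365 days". The weight mark is "Weigh loss at least 5% from baseline in ≥ 60% participants at the end of study". Weight is also measured at ablation (same section, and Table 1 at week 13), but no mark is attached to that measurement.

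Statistical analysis counts a "total cumulative dose of 657 mg of liraglutide or more over 52-week follow-up period". For weight it says: "The percentage of change in weight from baseline to the end of follow-up will be calculated for each participant", followed by the proportions above and below 5%. Under Intervention, dosing starts at 0.6 mg daily and rises weekly "up to a maintenance dose of 3 mg once daily, or the maximally tolerated".

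**The concern.** The drug is studied as a bridge to ablation, so what has to be learned is whether patients take it, and lose weight, during the wait. The rule that decides feasibility asks neither question. A single dose total lets later doses stand in for missing early ones, or early doses for missing later ones, depending on the window. The weight mark can be met by loss that occurs entirely after the procedure.

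The study could therefore meet its adherence and weight marks without showing that the premise of the definitive trial holds. The stated analysis would also leave out one of the two weight results that the primary objective calls for.

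**Working it through.** **Reproducing the plan's figures.** 1.8 mg × 365 days = 657 mg, as stated. The exact 95% interval for 21 of 30 is 50.6% to 85.3%, or 15.2 to 25.6 participants, which agrees with the 15–25 in Justification of sample size.

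**Inputs.** Ablation at day 91 (13 weeks), then 364 days of treatment (52 weeks), 455 days in all. Weekly steps start at 0.6 mg; the step size is not stated, so 0.6 mg is assumed. No doses are missed once treatment starts. The dose total could be counted over three windows:
- A: the 364 days after ablation, the literal reading of Statistical analysis;
- B: the first 365 days from baseline;
- C: all 455 days.

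**No drug before ablation, titration from day 91.** A and C leave 364 dosing days; B leaves 365 − 91 = 274.

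| Maintenance | Titration | A and C | B |
|---|---|---|---|
| 3 mg | 7 × (0.6+1.2+1.8+2.4) = 42 mg in 28 days | 42 + 336 × 3 = 1050 mg | 42 + 246 × 3 = 780 mg |
| 2.4 mg | 7 × (0.6+1.2+1.8) = 25.2 mg in 21 days | 25.2 + 343 × 2.4 = 848.4 mg | 25.2 + 253 × 2.4 = 632.4 mg |
| 1.8 mg | 7 × (0.6+1.2) = 12.6 mg in 14 days | 12.6 + 350 × 1.8 = 642.6 mg | 12.6 + 260 × 1.8 = 480.6 mg |

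At 3 mg the participant passes 657 mg under every window. With 0.3 mg steps the 3 mg totals are 1016 and 746 mg, and at a flat 3 mg they are 1092 and 822 mg, so the result does not hang on the step size. At 2.4 mg the participant passes under A and C and fails under B. At 1.8 mg the participant fails throughout.

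**Does the missing pre-ablation drug cause the 1.8 mg failures?** Full dosing at 1.8 mg gives:
- A: 364 × 1.8 = 655.2 mg, a fail;
- B: 12.6 + 351 × 1.8 = 644.4 mg, a fail;
- C: 12.6 + 441 × 1.8 = 806.4 mg, a pass.

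So at exactly 1.8 mg, pre-ablation doses decide the result only under C.

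**Stopping early, doses counted from baseline (B or C).** A participant on 3 mg reaches 657 mg after 28 + (657 − 42)/3 = 233 days, which is 142 days, or about 20 weeks, after ablation. Nothing taken in the remaining 455 − 233 = 222 days alters the classification.

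**Slack over 65 weeks.** The full schedule is 42 + 427 × 3 = 1323 mg, and 1323 − 657 = 666 mg. The whole pre-ablation dose is 42 + 63 × 3 = 231 mg, so the slack is 666/231 = 2.9 times that dose.

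**Weight.** The mark is 60% of 30 = 18 participants with at least 5% loss at week 65. Baseline and week-65 weights settle it; the ablation weight does not enter.

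**Phase totals on the plan's own 1.8 mg basis.** Before ablation, 12.6 + 77 × 1.8 = 151.2 mg over 91 days (142.8 mg with 0.3 mg steps; 163.8 mg with no titration allowance). After ablation, 364 × 1.8 = 655.2 mg.

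**The case against.** The best defence is that the adherence mark matches its own objective, which is framed at the end of the year after ablation, and that the Background asks for evidence, not for a pass mark in each phase. The definitive trial's endpoint also lies 52 weeks after ablation, so end-of-study marks are a defensible choice. This stands as an argument against demanding new thresholds. It does not answer the weight objective, which names ablation explicitly, or the Background's call for adherence on both sides of the procedure.

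It can also be said that pre-ablation data are not ignored. Weight is measured at ablation, monthly calls and pen returns track dosing from the start, and the Discussion part of the Abstract says that adherence and average weight loss will inform the later design. That is correct. A reader might infer that the study cannot examine the bridging period, or that a feasible result triggers the definitive trial; the documents support neither. What remains is that the stated rule and analysis do not use the data. The sentence in Statistical analysis about summaries before ablation is confined to secondary outcomes, and weight is a primary one. Nor is this only detail condensed out of an article, because the article states the criteria and the weight calculation explicitly.

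Finally, zero pre-ablation dosing is remote, since treatment starts at baseline and the design is at least 13 weeks of injections before ablation. This is fair. The example shows that there is no floor. It does not show that many of the 21 participants needed would behave this way.

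**Conclusion.** The point holds as a mismatch between what the protocol says it must learn and what its feasibility rule and stated analysis use. No pre-ablation result for dose or weight enters either. A participant with no drug before ablation who then titrates to 3 mg is adherent under every window (780 to 1050 mg against 657 mg). If counting starts at baseline, a 3 mg participant may stop on day 233 and still be adherent. These figures assume 0.6 mg steps, ablation at day 91 and no missed doses in the period of dosing.

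Two stronger readings should be resisted. One is that anyone who skips the pre-ablation phase still passes: at 2.4 mg that depends on the window, and at 1.8 mg the participant fails, in two of the three windows regardless of pre-ablation dosing. The other is that the 70% mark and the 5%-in-60% mark ought to apply at week 13. Both marks are stated for the end of the study, and the documents give no expected 13-week figure, so moving them could label a workable intervention infeasible. The change is worth making because it lets the study answer its own question from data already planned.

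**What to change.** In Statistical analysis:
- Compute percentage weight loss, and the proportion with at least 5% loss, at ablation as well as at week 65. Give the proportions exact 95% confidence intervals; for scale, 18 of 30 would be 41% to 77%.
- Report the proportion adherent separately before and after ablation on the 1.8 mg/day basis: about 151 mg over 91 days, scaled to the actual wait, and about 655 mg over the 364 days after. Give exact 95% confidence intervals for each.
- Record whether the participant is still injecting at the ablation and week-65 visits.

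In Feasibility outcome measures, state that the feasibility conclusion will consider these pre-ablation results alongside the existing marks. Whether to add a numeric week-13 mark, and at what level, is for the sponsor.

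The cost is a little more analysis and a possibly less favourable feasibility picture. Weight at ablation, monthly calls and pen returns are already planned, and both visits are in Table 1. Phase totals still permit some offsetting within a phase: at 3 mg, 151.2 mg is reached on day 65 of 91 (28 + (151.2 − 42)/3 = 64.4), and 655.2 mg about 219 days after ablation (655.2/3 = 218.4). The still-injecting record exposes early stopping but not mid-phase gaps.

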## Methods and design

### Study design and population

This is an open-label, uncontrolled, prospective, single-centre feasibility study of liraglutide in the treatment of obese AF patients injected for at least 13 weeks before and 52 weeks after AF ablation. Patients waiting for first-time AF ablation in QEHB will be invited for the study. We aim to recruit 30 patients who meet the eligibility criteria. Potential participants will be screened through cardiology outpatient clinics and the waiting list for AF ablation at QEHB.

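### The 657 mg adherence cut-off has no stated start date in one section and a post-ablation window in another, so whether pre-ablation doses count is not consistently fixed

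*Protocol article*

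**What the plan says.** All references are to the protocol article.

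- **Study design and population:** liraglutide is "injected for at least 13 weeks before and 52 weeks after AF ablation", so treatment lasts at least 65 weeks.
- **Feasibility outcome measures:** the target is "Adherence to medication rate ≥ 70% in the participants at the end of study". The next sentence measures adherence by a total of 657 mg "and more of liraglutide at 1 year", and derives that figure from 1.8 mg a day for 365 days. The year has no stated start.
- **Statistical analysis:** adherence is the proportion who tolerate a "total cumulative dose of 657 mg of liraglutide or more over 52-week follow-up period". The mean and standard deviation of cumulative dose are also to be reported, with no window given.
- **Aims and objectives** and **Justification of sample size:** the first asks for adherence until the end of the 52 weeks after ablation. The second expects 70% (21 of 30) to be adherent, with the interval given at 52 weeks following ablation.
- **Intervention:** "This will be reported as cumulative doses of liraglutide over the study period". No 657 mg cut-off is attached to this total.

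**The concern.** A cumulative-dose criterion needs a start and an end, because every day inside the window adds to the sum. Here the same 657 mg is tied to a year with no start in one section and to the post-ablation follow-up in another, within a course longer than either. If the year is counted from first dose, or the end-of-study wording is taken as the window, pre-ablation doses count. If the follow-up is the window, they do not.

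Adherence is one of three primary objectives and has a pass mark. The Background section says the definitive trial cannot be designed without evidence that adherence is maintained both before and after ablation. A pooled sum would let pre-ablation dosing stand in for post-ablation adherence. In an open-label study, that choice should not remain open until the data are seen.

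**Working it through.** **Inputs.** The 657 mg cut-off, 1.8 mg and 365 days come from Feasibility outcome measures. The course of 13 + 52 weeks (91 + 364 = 455 days) comes from Study design and population. The schedule comes from Intervention: "liraglutide will be injected 0.6 mg once daily, increased in steps of 1 week up to a maintenance dose of 3 mg once daily". A lower ceiling applies where 3 mg is not tolerated. Three assumptions are mine, for illustration only: steps of 0.6 mg, no missed doses before stopping, and a lead-in of exactly 13 weeks.

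**1. The plan's own figures.** 1.8 × 365 = 657.0 mg, which reproduces the cut-off. The exact binomial 95% interval for 21 of 30 is 50.6% to 85.3%, or 15.2 to 25.6 participants, in line with the stated 15–25. Neither is in error.

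**2. Pre-ablation dose over 91 days.**
- Ceiling 3 mg: 7 × (0.6 + 1.2 + 1.8 + 2.4) + 63 × 3 = 42 + 189 = 231.0 mg
- Ceiling 2.4 mg: 7 × (0.6 + 1.2 + 1.8) + 70 × 2.4 = 25.2 + 168 = 193.2 mg
- Ceiling 1.8 mg: 7 × (0.6 + 1.2) + 77 × 1.8 = 12.6 + 138.6 = 151.2 mg

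These are 23% to 35% of 657 mg.

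**3. When a participant at 3 mg reaches 657 mg.**
- Counting from first dose: 28 + (657 − 42)/3 = 28 + 205 = day 233 (week 33.3, about 20 weeks after ablation).
- Counting from ablation: 91 + 657/3 = 91 + 219 = day 310 (week 44.3).

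A participant who stops between these days, a band of 77 days or 11 weeks, changes status with the window. One who stops on day 233 has 657 mg in all but only 657 − 231 = 426 mg after ablation.

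**4. A fully compliant participant with a 1.8 mg ceiling**, the dose from which 657 mg is derived:

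| Window | Sum (mg) | Adherent? |
|---|---|---|
| 365 days from first dose | 12.6 + 351 × 1.8 = 644.4 | No |
| 364 days (52 weeks) after ablation | 364 × 1.8 = 655.2 | No |
| 365 days after ablation | 657.0 | Yes |
| Whole 65 weeks | 151.2 + 655.2 = 806.4 | Yes |

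**5. Effect on the 70% verdict.** Assume that all participants reach 3 mg, 70% are still on treatment at day 455, and the other 30% stop either evenly over time or at a constant rate.
- Even stopping: adherent share 1 − 0.3 × 233/455 = 84.6% if pre-ablation doses count, and 1 − 0.3 × 310/455 = 79.6% if not.
- Constant rate: 0.7^(233/455) = 83.3% and 0.7^(310/455) = 78.4%.

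The difference is 30 × 0.051 = 1.5 participants in each case, to one decimal (30 × 0.049 for the constant rate). By the binomial distribution, the probability of at least 21 of 30 is 98.9% against 93.1% (even) and 98.0% against 90.6% (constant rate). Under these assumptions anyone adherent on the post-ablation window is also adherent on the longer one. The gap of 6 to 7 percentage points is therefore the share of studies whose verdict changes.

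**The case against.** The strongest reply is that the two statements of the cut-off can be read as one window. A year and 52 weeks differ by a day, and Aims and objectives, Justification of sample size and Statistical analysis all point to the period after ablation. No section states a clock that starts at first dose. This largely stands: a post-ablation year is the most natural reconciliation and is what the fix adopts. But Feasibility outcome measures does not say so, and it adds an end-of-study time point to the same criterion. The single day is not harmless either, as step 4 shows.

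A reader might infer that 657 mg is applied to three windows, including the whole 65 weeks, which would lower the required average to 657/455 = 1.44 mg a day. The documents do not support that. The cut-off appears in two places only, and the whole-study total under Intervention is a reporting statement that can sit beside a one-year criterion.

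It is also fair that a condensed article may leave exact clock dates to the full documents. The point here is narrower: the article does state the criterion and its analysis, and the two wordings do not fix the same window.

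**Conclusion.** The point holds as an inconsistency of wording in a primary criterion. Whether pre-ablation doses count toward 657 mg is not consistently fixed, and the answer changes who is adherent. Under the assumed schedule, the participants affected at 3 mg are those who stop between about weeks 33 and 44 from first dose. The lead-in is stated as a minimum, and a longer one would widen that band.

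The likely effect on the overall verdict is modest: about 1.5 of 30 participants, with expected adherence above 70% on either window. A reader might infer that the feasibility decision hinges on this choice. The figures do not support that, since the verdict is unchanged in some 93% to 94% of studies under the assumed pattern. They also rest on every participant reaching 3 mg without interruption, whereas the Intervention section allows a lower tolerated dose and foresees disruption. No view is taken on the dose threshold.

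**What to change.** Reconcile Feasibility outcome measures and Statistical analysis to one window: from the day of ablation to the end of the 52-week follow-up, as Aims and objectives and Justification of sample size already imply. Count only doses in that window toward the criterion. Report the pre-ablation cumulative dose and the whole-study total separately, as descriptive figures. The first gives the pre-ablation adherence that the Background section asks for.

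State the window's length in days so that it matches the 365 days from which 657 mg was derived. With 364 days and an unchanged cut-off, a fully compliant participant at 1.8 mg would fail with 655.2 mg. The threshold itself is for the investigators.

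The cost is mainly wording. The reported adherence figure may be slightly less favourable. Dose from the monthly calls and returned pens will have to be split at the ablation date, and the article does not show that these sources record dose by date, so the split needs to be arranged.

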### Secondary outcome measures

#### Recurrence of AF

Recurrence of AF is defined as a heart rhythm with no discernible p waves and irregular RR intervals, when atrioventricular conduction is not impaired on a standard 12 lead ECG or a recording of a single-lead ECG tracing of equal or more than 30 s, by Kardia recording. Recurrence will be determined time-to-first recurrence after a 12-week blanking period (> 30-s AF, secondary end point).

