### Aims and objectives

The primary aim of this feasibility study is to determine whether liraglutide injected 3 mg once daily for 13 weeks before first-time AF ablation and continued for 52 weeks after ablation is a feasible method of reducing the recurrence and burden of AF (reported as percentage of total recordings) detected by Kardia portable electrocardiogram (ECG) recordings (at least twice a day and according to symptom-triggered recordings) after catheter ablation in patients with paroxysmal or persistent AF and body mass index above 30. In our centre (Queen Elizabeth Hospital, Birmingham, QEHB), the usual waiting time for patients for their first-time ablation is at least 12 weeks. A shorter waiting time is unusual in the United Kingdom (UK), and a longer waiting time needs to be avoided, as delay increases risk of AF recurrence.

Feasibility (the primary objectives) of the study will be determined by the measurement of the following:The number of participants recruited as a proportion of those eligible for the study over the recruitment periodThe proportion of participants adherent to liraglutide until the end of 52 weeks follow-up after ablationThe percentage of weight loss (from recruitment) achieved at the time of ablation and the end of follow-up period after ablation.

Exploratory outcomes will also be determined as follows:The proportion of participants adherent to Kardia recording requirements (at least twice daily recordings over 52 weeks)The time-to-first recurrence of AF (> 30 s) beyond 12-week blanking period post ablationThe burden of AF (percentage of total observed time) beyond 12-week blanking period post ablation in predefined periods (13th–26th weeks, 27th–39th weeks, and 40th–52nd weeks following ablation)Changes in cardiac MRI (CMR) measures from baseline to before ablation◦ Epicardial adiposity (volume measure in cm^3^)◦ Left atrial fibrosis (percentage of scar to total atrial volume rendered in CEMERGAPP by using late gadolinium-enhanced left atrial CMR images)Changes in fibroblast growth factor (FGF)-23 (pg/ml) and bone morphogenic protein (BMP)-10 (ng/ml) levels from baseline to before ablationChanges in electro-anatomic mapping data (right atrial bipolar voltage [mV] and conduction velocity [cm/s]), from baseline to before ablation

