#### AF burden

AF burden will be quantified by twice daily and symptom-triggered (onset and termination) Kardia recordings which will be sent daily. The time of the recorded AF event will be taken as the onset of the episode, with the next recorded sinus rhythm taken as the offset.

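### Sustained regular flutter or atrial tachycardia is event-free on the recurrence curve, and in time-based burden it scores zero or counts as AF depending on whether an AF trace came just before

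*Protocol article*

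**What the plan says.** **Recurrence.** The section on recurrence of AF gives an explicit ECG criterion, on a 12-lead ECG or a Kardia trace of at least 30 s: "Recurrence of AF is defined as a heart rhythm with no discernible p waves and irregular RR intervals, when atrioventricular conduction is not impaired". The timing rule is "Recurrence will be determined time-to-first recurrence after a 12-week blanking period (> 30-s AF, secondary end point)". Flutter and atrial tachycardia are not mentioned anywhere in the article.

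**Burden.** The AF burden section states that "AF burden will be quantified by twice daily and symptom-triggered (onset and termination) Kardia recordings". It fixes the start of an episode with "The time of the recorded AF event will be taken as the onset of the episode" and the end "with the next recorded sinus rhythm taken as the offset". Aims and objectives describes burden in two ways: once as "burden of AF (reported as percentage of total recordings)", and once, among the exploratory outcomes, as a percentage of total observed time in set windows after blanking.

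**Use.** Statistical analysis says "A Kaplan–Meier curve will be constructed for time to recurrence of AF at 1 year following ablation", in preparation for the sample size of the future trial. Background says that trial's primary outcome "will be the effect on AF-free survival at 52 weeks following AF ablation". The Discussion adds that this study is to show whether AF burden or recurrence at 52 weeks is suitable as that trial's primary endpoint.

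**The concern.** The written rules recognise two rhythms, AF and sinus rhythm. A third rhythm that is neither falls between them, and each outcome deals with it by accident.

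For recurrence, a sustained regular flutter or tachycardia does not meet the criterion, so the patient stays event-free although sinus rhythm has been lost. The Background presents maintenance of sinus rhythm as the purpose of rhythm control. Read as a measure of that, the curve can only err in the favourable direction.

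For time-based burden, opening needs AF and closing needs sinus rhythm. Flutter can do neither. Whether a stretch of flutter counts therefore depends on the trace recorded before it, not on the flutter itself.

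At stake is what the study hands to the next trial. Testing these two endpoints is a stated purpose of the work, although they are secondary or exploratory here.

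**Working it through.** **The plan's own figures.** The article gives no event rate, sample size or precision for recurrence or burden, so there is nothing to reproduce on this point. Its one computed interval concerns adherence (21 of 30). The exact 95% interval is 50.6% to 85.3%, or 15.2 to 25.6 participants, which agrees with the stated 15–25. It has no bearing here.

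**Step 1: trace the rules over weeks 13–52.** Inputs from the article are two recordings a day, the recurrence criterion, and AF onset with sinus offset. The rhythm histories are hypothetical. There are 40 × 7 × 2 = 560 recordings.

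| History after blanking | Recurrence | Burden, % of time | Burden, % of recordings |
|---|---|---|---|
| A. Sinus rhythm, then regular flutter for the second half; no AF recorded | No | 0 | 0 |
| B. AF recorded during blanking, then flutter with no sinus trace to week 52 | No | 100, only if the open episode is carried past week 12 | 0 |
| C. Sinus rhythm, one AF trace halfway, then flutter to the end | Yes | 280/560 = 50 | 1/560 = 0.2 |
| D. As C, with one sinus trace between the AF and the flutter | Yes | 1/560 = 0.2 | 1/560 = 0.2 |

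C and D differ by one recording, yet time-based burden moves from 50% to 0.2%. The recordings-based column does not move.

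**Step 2: one predefined window.** Weeks 13–26 span 14 × 7 = 98 days. Take 14 days of flutter that end in sinus rhythm.
- No AF trace just before: 0/98 = 0%.
- One AF trace just before, with no sinus trace in between: 14/98 = 14.3%.

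**Step 3: size of the effect on the curve.** The article gives no figures, so two are assumed: 30% of patients have any atrial arrhythmia recurrence, and in 10% to 30% of those it is flutter or tachycardia only.
- AF-only rate: 0.30 × (1 − 0.10) = 27%; 0.30 × (1 − 0.30) = 21%.
- Events among 30 patients: 9 for any arrhythmia, against 8.1 to 6.3 for AF only, a difference of 0.9 to 2.7.
- Patients needed for a fixed number of events vary as 1/rate: 0.30/0.27 = 1.11 and 0.30/0.21 = 1.43. A definitive trial that counted every atrial arrhythmia but was sized on the AF-only rate would be 1.11 to 1.43 times larger than needed.

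**The case against.** The strongest reply is that AF-only recurrence is a coherent choice. The definitive trial's stated outcome is AF-free survival, and an AF-only curve is the matching input for it. The curve is labelled as recurrence of AF, not as loss of sinus rhythm. This stands: the definition is narrow, but it does not contradict the stated endpoint, and the AF-only curve should be kept.

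Three stronger readings are tempting, and the article does not support them.
- *The burden rule counts flutter as AF.* Not in general. An episode needs a recorded AF onset, so a patient with flutter alone scores zero on both outcomes (history A).
- *Recurrence and burden contradict each other in the same patient.* If the AF trace falls after blanking and meets the duration rule, recurrence is already counted (history C). A recurrence-free patient with positive burden arises only in history B, and the article does not say that an open episode is carried past week 12.
- *The next trial would be underpowered.* The arithmetic points the other way: a lower event rate leads to a larger trial.

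Other limits also stand. Only the observed-time version of burden is affected. Flutter with variable conduction can show irregular RR intervals and may meet the AF criterion, so the event-free result is certain only for regular rhythms. The effect is small beside the study's precision: the exact 95% interval for 9 of 30 is about 15% to 49%, which covers the whole assumed range.

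The suggestion that ECG classification belongs in a fuller document carries less weight. The onset and offset rules are written in this article, and it is those written rules that give the arbitrary result.

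**Conclusion.** The concern holds in two limited parts. First, the AF-only criterion leaves sustained regular flutter or tachycardia event-free on a curve intended to help size the next trial. On the assumed 30% recurrence and 10–30% flutter or tachycardia share, that is about 1 to 3 of 30 patients. Second, the asymmetric onset and offset rule makes time-based burden depend on the preceding trace: 0% or about 14% for the same 14 days of flutter in weeks 13–26. The second part follows from the written rules and needs no assumed event rate.

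Neither part touches the feasibility criteria, which concern recruitment, drop-out, data completeness, adherence and weight loss. The change is still worth making, because these outcomes are being tried out for the definitive trial.

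**What to change.** Use one rhythm classification (sinus rhythm, AF, flutter or atrial tachycardia) for every 12-lead and Kardia trace, and apply it to both outcomes.

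- **Recurrence.** Report time to first AF, flutter or atrial tachycardia of the stated duration after blanking, beside the AF-only curve that matches AF-free survival. The next trial can then be sized on either.
- **Time-based burden.** Make onset and offset symmetric. Either any atrial arrhythmia opens an episode and sinus rhythm closes it, or only AF opens it and any non-AF trace closes it. The first option gives about 14% in both cases of the 14-day example. Under the second, flutter adds no burden beyond the interval to the next trace. State also whether an episode open at the end of blanking is carried forward.

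The cost is wording and labelling of traces already collected. There are two downsides: the reported success rate will look slightly less favourable on the wider definition, and some regular tachycardias will be hard to label from a single lead.
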